## Abstract

**Background:**

Emotional disorders (ED) are among the most prevalent mental disorders. However, less than 50% of people suffering from ED receive the appropriate treatment. This situation has led to the development of new intervention proposals based on the transdiagnostic perspective, which tries to address the underlying processes common to ED. Most of these programs focus primarily on down-regulating negative affectivity, rather than increasing strengths and up-regulating positive affectivity. The data suggest the existence of disturbances in positive affectivity in these disorders, and so new interventions focusing on these problems are greatly needed. It is also essential to provide assistance to all the people in need. Information and Communication Technologies can be very useful. This study aims to evaluate the efficacy of a transdiagnostic Internet-based treatment for ED in a community sample. The protocol includes traditional CBT components, as well as a specific component to address positive affect. We intend to test this protocol, including this specific component or not, versus a waiting list control group. Moreover, we aim to test the differential effect of this specific component, and study the effectiveness (in terms of patients’ acceptance) of using a self-applied Internet-based program. This paper presents the study protocol.

**Methods:**

The study is a randomized controlled trial. 207 participants will be randomly assigned to: a)*Transdiagnostic Internet-based protocol (TIBP),* b)*Transdiagnostic Internet-based protocol + positive affect component (TIBP + PA),* or c)a Waiting List control group (WL). Primary outcomes measures will be the BDI-II, the BAI, and the PANAS. Secondary outcomes will include diagnosis-specific measures of the principal disorder. Participants’ treatment acceptance will also be measured. Participants will be assessed at pre-, post-treatment, and 3- and 12- month follow-ups. The data will be analyzed based on the Intention-to-treat principle. Per protocol analyses will also be performed.

**Discussion:**

To the best of our knowledge, this is the first study of a transdiagnostic Internet-based treatment for ED with a specific component to up-regulate positive affectivity. This intervention could contribute to improve the efficiency and effectiveness of current treatment programs for ED, promote the dissemination of EBTs, and help to decrease the high prevalence of ED.

**Trial registration:**

ClinicalTrial.gov: NCT02578758. Registered 15 October 2015.

## Background

### Introduction

Lifetime prevalence estimates for emotional disorders (ED), defined as anxiety and unipolar mood disorders, are quite high (anxiety disorders, 28.8%; mood disorders, 20.8%), with comorbidity rates ranging between 40 and 80% [1]. These disorders disrupt the lives of millions of people each year, and they are one of the main causes of disability worldwide [2, 3].

In the past few decades, evidence-based psychological treatments (EBTs) have been shown to be effective in the treatment of ED [4]. This development can be considered a significant advance in addressing the large worldwide treatment needs [5]. However, the scale of these treatments is not sufficient to reduce the disease burden of mental disorders [6]. Less than 50% of people suffering from ED receive adequate treatment [7], and this percentage is much lower in adolescents, older adults, people with a lower socio-economic status, and people from ethnic minorities [8].

These low levels of successful dissemination of EBTs can be explained by their costs, the duration of the treatments, and the lack of well-qualified professionals [9]. This is especially problematic in everyday clinical practice and can explain why EBTs are under-utilized [10]. It is not surprising, therefore, that this continued lack of widespread availability of EBTs has raised the need to implement innovative and even radical solutions to ensure that the aid reaches all those in need [8, 11, 12]. There is a compelling need for approaches that go beyond “one-to-one” psychotherapy (either with a patient, a family, or a group) and develop a new portfolio to administer EBTs [6].

Different EBTs targeting specific anxiety and mood disorders have been developed [13–16]. Each diagnosis-specific treatment manual requires the use of separate handbooks, workbook, and protocols, and therapists must be trained in the use of each of them, which may hinder widespread dissemination of EBTs [9].

In recent years, new proposals have emerged for transdiagnostic treatments that emphasize the essential processes underlying different disorders. In the field of ED, studies emphasize that these disorders share important characteristics, and that this overlap emerges from common biological and psychological vulnerabilities [14, 17, 18]. Barlow summarizes the commonalities in the etiology of ED in the model referred to as “triple vulnerabilities”. This theory encompasses a generalized biological vulnerability (involving nonspecific genetic contributions to the development of anxiety and negative affect), a generalized psychological vulnerability (associated with early life experiences under certain conditions), and a specific psychological vulnerability emerging from early learning [14]. There is evidence that the two generalized vulnerabilities are involved in the development and expression of the ED [18, 19].

People with ED have higher levels of neuroticism/negative affect/behavioral inhibition (N/NA/BI) [18], and they experience negative emotions more intensely and frequently [20, 21], accept emotional experiences to a lesser extent [22], associate the experience of living with more negative emotions [23], use cognitive and behavioral strategies to reduce the impact of negative emotions [24], and show intolerance to uncertainty, leading to an increase in negative affect [25]. In short, people with ED tend to react negatively to their emotions and are more likely to use maladaptive emotion regulation strategies. These strategies, in turn, increase the frequency/intensity of negative emotions. Some authors have argued that this functional relationship may be driven by neuroticism, which would be the core of the ED [26].

By contrast, the role of extraversion/positive affect/behavioral activation (E/PA/BA) in ED has also been pointed out. A meta-analysis indicated that most individuals with an ED show low levels of E/BA [27]. The data suggest that alterations in PA are observed in many disorders [28]. Low levels of PA predict the onset of depression [29], dampen positive emotions, are maladaptive, and increase the severity of the problem [30], whereas high PA is associated with better health, both physical and psychological, and greater well-being [31]. Despite the importance of disturbances in positive affectivity in ED, few studies focus on promoting PA.

Based on the transdiagnostic perspective, Barlow’s team designed the Unified Protocol (UP): a transdiagnostic, emotion-focused, cognitive-behavioral treatment for ED that emphasizes the role of emotion regulation [9, 26, 32]. The UP focuses on four essential aspects that have the general purpose of down-regulating NA: addressing emotional avoidance, promoting cognitive flexibility, and facilitating exposure to avoided situations and sensations. Moreover, it places special emphasis on increasing present-focused emotional awareness. The UP has been tested, and results indicate that it is effective [33], with improvements maintained at 18-month follow-up [34]. Moreover, the effect of the UP has been shown on the two temperament dimensions of N/BI and E/BA [35].

The data suggest that a transdiagnostic treatment for ED might be more widely effective across diverse mental health problems, in other words, treatments aimed at addressing different disorders with a single protocol [36]. Some meta-analyses have been conducted on the efficacy of transdiagnostic protocols for anxiety disorders [37] and for anxiety and/or depression [38–40].

Nevertheless, these transdiagnostic protocols have focused on reducing NA, but less attention has been paid to promoting PA or modifying risk factors. As the World Health Organization’s definition of mental health expresses, mental health is more than just the absence of mental illness [41]. It is not surprising, therefore, that well-being and positive functioning are considered core elements of mental health. As Southwick and Charney [42] point out, the use of procedures to promote resilience (such as positive emotions and optimism) can be useful in the treating ED and in generating protective factors. The benefits may be associated with a reduction in the risk of developing mental symptoms and disorders [43, 44]. However, as stated above, interventions that include components to up-regulate PA have been missing or very scarce in the clinical setting.

Taking all this into consideration, it is necessary to develop and test treatment components focused on enhancing protective factors and resilience and mitigating risk factors. Literature has highlighted the potential importance of positive emotionality as a treatment component [45, 46].

To date, the dominant delivery format in psychotherapy has been individual face-to-face contact; however, it is much more expensive and time-consuming than other formats, such as guided self-help and Internet-based treatments [47]. Recently, research has shown that Information and Communication Technologies (ICT) can facilitate the availability of EBTs [6, 48, 49]. Specifically, some literature suggests that the Internet can be used for the assessment and treatment of clinical conditions [50]. Internet-based treatments are interventions conducted over the Internet with more or less therapist involvement and support [51]. The evidence strongly suggests that Internet-based treatments are effective in the treatment of depression and anxiety disorders [52]. Moreover, data from meta-analyses reveal that these interventions are as efficacious as face-to-face traditional treatments [53–55].

We have developed an online psychological treatment protocol for individuals with a diagnosis of ED [56], major depression disorder (MDD), dysthymic disorder (DD), obsessive-compulsive disorder (OCD), and four anxiety disorders: panic disorder (PD), agoraphobia (AG), generalized anxiety disorder (GAD), social anxiety disorder (SAD), anxiety disorder not otherwise specified (ADNOS), and (unipolar) mood disorder not otherwise specified (MDNOS).

This treatment protocol includes two types of components: one based on classical perspectives for down-regulating NA and the other aimed at up-regulating PA. The protocol can be applied either in its traditional format (*Transdiagnostic Internet-based Protocol –TIBP–)* or by including both of these components (*Transdiagnostic Internet-based Protocol + Positive Affect Component –TIBP + PA–*). Moreover, we have developed an adaptation of the treatment protocol that can be applied online over the Internet. We can thus reach community samples, that is, people who suffer from an ED but are not receiving primary or specialized care.

We intend to study the effect of both treatments in terms of efficacy for depressive and anxious symptomatology. Moreover, we aim to assess the effects of the specific treatment component designed for up-regulating PA. Finally, the effectiveness of the Internet-based program developed to apply the treatment protocol over the Internet with minimal support by the clinician will be studied. We hypothesize that: a) both self-applied protocol modalities (*TIBP* and *TIBP + PA*) will be more effective than the waiting list control condition in the treatment of ED; b) both interventions will result in significant improvements in depressive and anxious symptomatology at post- treatment, and these results will be maintained at 3- and 12- month follow-ups; c) the *TIBP + PA* will significantly outperform the *TIBP* group on PA measures; and d) both protocols will be well accepted, with no statistical differences between conditions. In this article, we present the study protocol.

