#### Transdiagnostic Internet-based protocol (TIBP)

This intervention protocol consists of twelve more traditional modules mainly designed to down-regulate NA. Each module has specific objectives:
*M1. Emotional disorders and emotion regulation.* The purpose of this module is to provide information about the central role of emotion regulation in emotional disorders. Brief descriptions of the program modules, as well as videos with examples of people suffering from different ED, are also presented.
*M2. Motivation for change.* The objective of this module is to enhance motivation for change by recognizing that attitudes towards change can be ambivalent and that motivation fluctuates. The main objective is to analyze the advantages and disadvantages of changing, emphasize the importance of being motivated, and highlight the importance of establishing significant life goals.
*M3. Understanding the role of emotions.* This module provides information about the adaptive roles and functions of emotions. It also shows the three-component model of emotions.
*M4. The acceptance of emotional experiences.* This module focuses on the awareness and role of acceptance of emotional experiences, as well as their importance in the treatment.
*M5. Practicing acceptance.* The objective of this module is to continue to learn about the acceptance of emotional experiences and increase awareness of physical sensations, thoughts, emotions, and daily activities.
*M6. Learning to be flexible.* This module teaches participants to be more cognitively flexible in order to see life situations from different perspectives, showing the importance of maladaptive ways of thinking and learning how to identify them in the maintenance of emotional disorders.
*M7. Practicing cognitive flexibility.* This module aims to teach the patients how to modify maladaptive ways of thinking. It also provides information about intrusive thoughts and how to deal with them.
*M8. Emotional avoidance.* The aim is to teach the patients emotion avoidance strategies that contribute to the maintenance of emotional disorders.
*M9. Emotion Driven Behaviors (EDBs).* The aim is for patients to learn the concept of EDBs and replace their own maladaptive EDBs with other more adaptive behaviors.

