#### Transdiagnostic Internet-based protocol + positive affect component (TIBP + PA)

This intervention protocol is made up of 16 therapeutic modules. The first 12 modules have been described above in the first condition *- (TIBP) -* and the other 4 are aimed to up-regulate PA by understanding and capturing positive emotions, and training adaptive positive emotion regulation strategies. These four modules are described as follows:
*M12. Learning to move on.* This module focuses on the role of behavioral activation. The aim is to teach the importance of ‘moving on’ in acquiring a proper level of activity and involvement in life. It motivates the patient to get involved in meaningful activities and become engaged in his/her life.
*M13. Learning to enjoy.* This module helps the patient to see the importance of positive emotions and teaches procedures that generate positive experiences, promoting involvement in pleasant and significant activities and contact with others. This module involves enjoying positive experiences and “savoring” positive aspects of life in order to enhance wellbeing.
*M14. Learning to live.* This module takes a further step in enhancing PA, understanding the importance of identifying the individual’s own psychological strengths, and selecting and carrying out meaningful activities linked to values and goals in life. This module provides strategies to achieve psychological well-being and resilience. The aim is to improve the individual’ abilities and live a life full of purpose and meaning.
*M15. Living and learning.* This module focuses on developing an action plan to boost the individual’s psychological strengths. It focuses on the importance of developing and enhancing one’s own strengths and starting to work for life and the future.
*M16. Relapse prevention (this module is the same for both conditions: (TIBP) and (TIBP + PA).* It aims to strengthen the strategies learned throughout the program, schedule future practice, and teach how to identify and cope with future high- risk situations.

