### Adaptation to the web

This protocol has been adapted to a multimedia web platform (video, images, etc.) and can be applied over the Internet (https://www.psicologiaytecnologia.com/). It is developed for optimal use on a PC or a tablet, and it allows individuals to do the modules from their home and at their own pace. The ease of use of the program has been strengthened because it presents a streamlined navigation, which allows users with less experience in handling new technologies to know where they are and how to keep moving forward at any time. The web adaptation of the protocol is the same in both conditions (TIBP and TIBP + PA), with the only difference being the inclusion or not of the modules that contain the PA-regulation component.

Duration of the program can vary among users, and participants in both treatment conditions have access to the protocol for a maximum period of 18 weeks. The program recommends working on one module for at least one entire week, and it sends messages encouraging the patient to continue to work to benefit from it. In both conditions, the modules include exercises and tasks to practice each technique and skill. Moreover, the platform is ready to welcome all participants with information about the treatment and its objectives, as well as general information and recommendations about how to benefit from it.

Regarding the assessment of patients within the program, after the “Welcome”, initial online questionnaires are presented as the pre-treatment assessment. In addition, post-module brief questionnaires to evaluate anxiety, depression, and positive/negative affect (OASIS, ODSIS, PANAS) are also filled out throughout the program. A noteworthy aspect of the program is that it allows the therapist to have access to all this information and receive an alert if the patient’s condition worsens. The program includes suicide risk alarms that consist of an email to the clinical team with information about a high risk of suicide. These alarms are generated when the system detects that the participant rated high on the suicidal ideation items. It allows the clinician to contact the patient and evaluate the actions that should be taken to protect him/her. Finally, after the treatment, the participants complete the online assessment in the post- and follow-up periods.

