#### Expectation of treatment scale and opinion of treatment scale.

The Expectation of Treatment Scale and Opinion of Treatment Scale are questionnaires adapted from Borkovec and Nau [96]. Each scale contains five items, rated from 0 (“strongly disagree”) to 10 (“strongly agree”), which cover how logical the treatment seemed, to what extent it could satisfy the patient, whether it could be used to treat other psychological problems, and its usefulness for the patient’s specific problem. The expectation scale is applied once the intervention has been explained, at the end of the “Welcome module”. This scale measures the patient’s subjective expectations about the treatment. In addition, the opinion scale is administered when the patient has completed the treatment, and its aim is to assess satisfaction with the intervention. Our group has used this questionnaire in several research studies [48, 97].

The study measures and assessment times are summarized in Table 2.

**Table 2 Tab2:** Study measures and assessment times

Measure	Aim	Time of assessment
MINI Neuropsychiatric Interview	Diagnosis	BL, Post-T and FU
PANAS	Positive and negative affect	Post-T and Post-module
BDI-II	Severity of depression	BL, Post-T and FU
BAI	Severity of anxiety	BL, Post-T and FU
OCI-R	Severity of OCD symptoms	BL, Post-T and FU
PDSS-SR	Severity of PD and agoraphobia symptoms	BL, Post-T and FU
PSWQ	Severity of GAD symptoms	BL, Post-T and FU
SIAS	Severity of SAD symptoms	BL, Post-T and FU
NEO FFI	Neuroticism and Extraversion	BL, Post-T and FU
EQ-5D	Health-related quality of life	BL, Post-T and FU
OASIS	Severity of anxiety	Post-module
ODSIS	Severity of depression	Post-module
Suicide item	Suicidal ideation	BL, Post-module, Post-T and FU
Expectation of Treatment Scale	Expectation of treatment	BL
Opinion of Treatment Scale	Opinion of treatment	Post-T

*BL*, Baseline; *Post-T*, post-treatment; *FU*, follow-ups, 3 and 12-month follow-ups; *PANAS*, Positive and Negative Affect Scale; *BDI-II*, Beck Depression Inventory-II; *BAI*, Beck Anxiety Inventory; *OCI-R*, Obsessive-Compulsive Inventory-Revised; *PDSS-SR*, Self-Reported Panic Disorder Severity Scale; *PSWQ*, Penn State Worry Questionnaire; *SIAS*, Social Interaction Anxiety Scale; *NEO FFI*, NEO-Five Factor Inventory; *EQ-5D*, EuroQoL-5D questionnaire; *OASIS*, Overall Anxiety Severity and Impairment Scale; *ODSIS*, Overall Depression Severity and Impairment Scale

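### Hypothesis (d) predicts no statistical difference in acceptance without a margin, so imprecision favours it, and the text and Table 2 leave unclear whether non-finishers rate the treatment

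*Protocol article*

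**What the plan says.** The last of the four hypotheses, in the Introduction of the protocol article, is that "both protocols will be well accepted, with no statistical differences between conditions". The conditions compared are the two active arms, TIBP and TIBP + PA. The article gives no margin for what would count as similar acceptance. Its Data analyses section describes F-tests on post-test means followed by Tukey or Games-Howell comparisons, mixed-effect models for the intention-to-treat analysis, and standardised effect sizes.

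Acceptance after use is measured by the Opinion of Treatment Scale, five items rated 0 to 10. The text says that "the opinion scale is administered when the patient has completed the treatment, and its aim is to assess satisfaction with the intervention". Table 2 lists the same scale at Post-T, the time point it also uses for the BDI-II and BAI. The companion Expectation scale does not measure acceptance after use: "The expectation scale is applied once the intervention has been explained", at the end of the Welcome module.

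The arms differ in length. For TIBP, "This intervention protocol consists of twelve more traditional modules"; for TIBP + PA, "This intervention protocol is made up of 16 therapeutic modules". Under Adaptation to the web, participants in both arms "have access to the protocol for a maximum period of 18 weeks", and the program recommends at least a week per module. The Sample size section expects 30% dropout.

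**The concern.** A hypothesis of no statistical difference is met by failing to reject. Small numbers, noisy ratings and dropout all make that more likely, so the weaker the data, the better the hypothesis fares. The other between-arm hypotheses, (a) and (c), predict superiority and are penalised by imprecision; (d) is helped by it.

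The second issue is who supplies the score. If only finishers rate, people who stopped because they disliked the program are absent from the comparison. Finishing asks for four more modules in TIBP + PA within the same access period, so the raters in the two arms may not be comparable even though randomisation made the arms comparable.

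Patient acceptance is a stated aim in the Abstract and again in the Discussion. At stake is a conclusion that adding the positive affect component costs nothing in acceptability.

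**Working it through.** **1. The plan's own sample size.** Inputs from Sample size: three groups, f = 0.25, alpha 0.05, power 0.80. With noncentrality N × f², N = 159 gives power 0.805, so the stated 159 (53 per group) is reproduced. The stated 207 equals 159 × 1.3, or 69 per group. This is a calculation for a medium difference among three arms. It was not designed to show similarity of two.

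**2. Raters per active arm.** 69 × 0.70 = 48.3, so about 48 (assumption: the 30% loss falls equally on both arms and applies to the Opinion score).

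**3. Precision.** The 95% half-width in SD units is t(0.975, 2n − 2) × √(2/n). With n = 48: 1.986 × 0.2041 = 0.405, about 0.41 SD. If all 69 per arm responded: 1.978 × 0.1703 = 0.337, about 0.34 SD.

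**4. Chance of a non-significant result when a difference exists.** Two-sided two-sample t-test, alpha 0.05, noncentrality d × √(n/2). The true d is not in the article, so a range is shown.

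| True difference (SD) | Missed, 48 per arm | Missed, 53 per arm | Missed, 69 per arm |
|---|---|---|---|
| 0.2 | 0.84 | 0.83 | 0.79 |
| 0.3 | 0.69 | 0.67 | 0.58 |
| 0.4 | 0.51 | 0.47 | 0.36 |
| 0.5 | 0.32 | 0.28 | 0.17 |
| 0.8 | 0.03 | 0.02 | 0.003 |

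**5. What a similarity claim could achieve.** With two one-sided tests (TOST) and no true difference, power is approximately 2Φ(m/√(2/n) − z) − 1. The margins m are assumptions.

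- One-sided alpha 0.05 (z = 1.645), n = 48: about 0 for m = 0.3 SD, 0.25 for 0.4 SD and 0.58 for 0.5 SD. For the last, 0.5/0.2041 = 2.449, less 1.645 is 0.804, and 2Φ(0.804) − 1 = 0.58.
- Same rule, n = 69, m = 0.5 SD: 0.80.
- Requiring the 95% interval to lie inside the margin is stricter (one-sided 0.025). At m = 0.5 SD, the t-based power is about 0.36 with 48 per arm and 0.66 with 69.

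**6. Who rates.** At the recommended pace TIBP needs at least 12 of the 18 weeks, leaving 6 spare, and TIBP + PA needs at least 16, leaving 2. Completion may therefore be harder in the longer arm, but the article gives no completion rates by arm.

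A simulation shows what unequal completion could do. It assumes a true 0.3 SD disadvantage in the longer arm and a correlation of 0.3 or 0.5 between opinion and the tendency to complete.

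| Completion, TIBP vs TIBP + PA (assumed) | Difference seen, correlation 0.3 | Difference seen, correlation 0.5 |
|---|---|---|
| 70% vs 70% | 0.30 SD | 0.30 SD |
| 75% vs 65% | 0.26 SD | 0.23 SD |
| 80% vs 60% | 0.21 SD | 0.15 SD |

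With equal completion the arm difference is undisturbed. With lower completion in the longer arm it shrinks towards the predicted null.

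**The case against.** The article states a prediction. It gives no rule that a non-significant test establishes equality, and it plans between-group effect sizes. Acceptance is not a primary outcome and does not drive the sample size. A margin might be left to an analysis plan that is not shown, and the article says the methods will be reviewed before analysis. All of this is fair, and it rules out saying that the plan treats non-significance as proof. It does not repair the hypothesis, which as worded is favoured by imprecision whatever a later document adds.

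A reader might infer that the favourable conclusion is close to guaranteed whatever the truth. The figures do not support that: with 48 raters per arm, a 0.5 SD difference would be detected about 68% of the time and a 0.8 SD difference about 97%. Nor does low power make the treatments well accepted in absolute terms, which is a separate part of (d).

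A reader might also infer that dropouts are not asked for their opinion. That rests on one phrase. Table 2 places the scale at Post-T, Adaptation to the web describes the post-treatment assessment without a module requirement, and Data analyses keeps the completers-only analysis separate from intention-to-treat. Having completed treatment could simply mean that the treatment period is over. What stands is an ambiguity to resolve.

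Differential completion is likewise plausible but undocumented. Sixteen weekly modules fit in 18 weeks, and the 30% is general loss during treatment, which need not equal failure to finish every module. The Discussion discloses the unequal module count and the equal time allowed, but as a limit on attributing an effect to the added component; it does not apply this to acceptability.

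**Conclusion.** The point holds in two parts of different strength.

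The first is firm. Without a margin, a finding of no statistical difference says little about similar acceptance when the interval extends about 0.41 SD either side and a 0.3 SD difference is missed about 69% of the time. This rests on about 48 raters per arm and a two-sample comparison. With all 69 responding, the 0.3 SD difference is still missed 58% of the time.

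The second is conditional. Read literally, the measures text limits raters to finishers of programs of different length; read with Table 2, it may not. If the literal reading applies and completion is lower in the longer arm, the observed difference could be pulled towards the null. The mixed model would help little, because the Opinion score is taken once, with no earlier value of itself. The documents do not show that this will occur.

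The change is worth making, since acceptance is a stated aim. The primary outcomes are not affected.

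**What to change.** - Reword (d): the difference between TIBP and TIBP + PA in Opinion score will be reported with its 95% confidence interval. Similar acceptability will be claimed only if that interval lies within a margin that the sponsor states and justifies in advance; otherwise the comparison will be called inconclusive.
- Reconcile the measures text with Table 2: give the Opinion scale at the Post-T assessment to all participants randomised to the two active arms, whatever number of modules they completed.
- Report modules completed and dropout by arm beside the Opinion score.

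The cost is one reworded hypothesis, one reworded measure description, and sending an existing five-item scale to people who did not finish. The real downside is that the similarity claim may well end inconclusive. For an assumed margin of 0.5 SD and no true difference, power with 48 per arm is about 0.58 by TOST at one-sided 0.05 and about 0.36 under the stricter 95% interval rule. Asking everyone helps: with all 69 per arm responding, these become 0.80 and 0.66.
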